## Abstract

**Background:**

The use of inhaled corticosteroid (ICS) medications has been shown to improve asthma control and reduce asthma-related morbidity and mortality. Two recent randomized trials demonstrated dramatic improvements in ICS adherence by monitoring adherence with electronic sensors and providing automated reminders to participants to take their ICS medications. Given their lower levels of adherence and higher levels of asthma-related emergency department (ED) visits, hospitalizations, and death, urban minority populations could potentially benefit greatly from these types of interventions.

**Objective:**

The principal objective of this study will be to evaluate the feasibility, acceptability, and limited efficacy of a text message (short message service, SMS) reminder intervention to enhance ICS adherence in an urban minority population of children with asthma. We will also assess trajectories of ICS adherence in the 2 months following asthma hospitalization.

**Methods:**

Participants will include 40 children aged 2-13 years, who are currently admitted to the Children’s Hospital of Philadelphia (CHOP) for asthma, and their parent or legal guardian. Participants will be assigned to intervention and control arms using a 1:1 randomization scheme. The intervention arm will receive daily text message reminders for a 30-day intervention phase following hospitalization. This will be followed by a 30-day follow-up phase, in which all participants may choose whether or not to receive the text messages. Feasibility will be assessed by measuring (1) retention of the participants through the study phases and (2) perceived usefulness, acceptability, and preferences regarding the intervention components. Limited efficacy outcomes will include percent adherence to prescribed ICS regimen measured using Propeller Health sensors and change in parent-reported asthma control. We will perform an exploratory analysis to assess for discrete trajectories of adherence using group-based trajectory modeling (GBTM).

**Results:**

Study enrollment began in December 2015 and the intervention and follow-up phases are ongoing. Results of the data analysis are expected to be available by December 2016.

**Conclusions:**

This study will add to the literature by providing foundational feasibility data on which elements of a mobile health text-message reminder intervention may need to be modified to suit the needs and constraints of high-risk urban minority populations.

**Trial Registration:**

Clinicaltrials.gov NCT02615743; https://www.clinicaltrials.gov/ct2/show/study/NCT02615743 (Archived with WebCite at http://www.webcitation.org/6ji59rAXN)

## Introduction

Asthma is the most common chronic medical condition in children in the United States, with 8.3% of children affected [1]. Racial disparities have long existed in both asthma prevalence and morbidity. Several reports from the last few years have demonstrated progress in narrowing the disparities gap in both asthma prevalence [1] and morbidity [2]. Despite this progress, black children with asthma still suffer significantly higher rates of asthma emergency department (ED) visits, hospitalizations, and death compared with their white peers [2].

Use of inhaled corticosteroid (ICS) medications has been shown to improve asthma control and reduce asthma-related exacerbations and hospitalizations [3-5]. Despite this evidence, average adherence to prescribed regimens for ICSs in childhood asthma is only around 50% of prescribed doses [6]. Several studies have demonstrated that adherence rates in urban minority populations in the United States are substantially lower, ranging from 11-37% [7-10]. Yet average rates may be misleading, as research from other studies indicates that patterns of day to day medication adherence are highly variable and these patterns change over time [11-13]. These studies capture the inter- and intra-individual variation in medication use and provide valuable information on the kinetics of different adherence trajectories [11-13]. Such studies may help identify the reasons behind adherence lapses, which, in turn, would allow providers to enhance and better tailor adherence intervention strategies.

Prior interventions to enhance daily medication adherence in children with chronic disease have generated modest, at best, improvements in adherence to recommended regimens [14-17]. However, 2 recent randomized trials from Australia and New Zealand demonstrated dramatic improvements in ICS adherence by monitoring adherence with electronic sensors and providing automated messages to remind participants to take their ICS medications [18,19]. Given their lower levels of adherence, urban minority populations could potentially benefit greatly from these types of interventions. Whether reminder-based interventions are feasible and effective in vulnerable urban populations in the United States, however, is unknown. The factors that drive nonadherence in inner city children with asthma appear more complicated than “just forgetting” [6,20,21]. For this reason, dedicated study of the feasibility and efficacy of automated reminder-based interventions may provide valuable information on how to design and tailor future interventions for this population.

The principal objective of this study will be to evaluate the feasibility, acceptability, and limited efficacy of daily text message (short message service, SMS) reminders as a means to improve adherence to ICS prescriptions in urban minority children with asthma in Philadelphia. We will also assess the longitudinal trajectories of ICS use following hospitalization and explore associations with factors previously associated with nonadherence.

## Methods

### Overview of Study

This is a pilot randomized controlled trial to assess the feasibility, acceptability, and limited efficacy of text message reminders for daily ICS medication use in high risk children with asthma. Subjects will include children seen in the ED or hospitalized for asthma at the Children’s Hospital of Philadelphia (CHOP) and their families. Propeller Health electronic sensors will be placed on ICS metered dose inhalers (MDI) at the time of ED or hospital discharge to measure subsequent medication use in both the intervention group and the regular care control group. The intervention group will receive text message reminders delivered to the caregiver’s mobile phone for 30 days following hospitalization. The protocol for the conduct of this study was approved by the CHOP institutional review board and is registered on ClinicalTrials.gov (NCT02615743).

### Setting

Subjects will be recruited from the ED and general pediatrics inpatient units at CHOP. CHOP is a large, free-standing, tertiary care children’s hospital that also serves as a community hospital for the children of Philadelphia, particularly in the west and southwest regions of the city. There are nearly 6000 ED visits and 2500 inpatient admissions for asthma at CHOP each year.

### Participants – Inclusion and Exclusion Criteria

Participants will include 40 children aged 2 to 13 years and their parent or legal guardian. To be enrolled in the study, children and their parent or legal guardian must meet the following eligibility criteria: (1) they must be receiving care for asthma on the ED or inpatient asthma pathways; (2) they must have been prescribed a daily ICS or combined ICS or long-acting beta agonist (LABA) in the year prior to the current admission and the ICS prescribed on discharge must be an MDI compatible with the electronic monitoring sensor (compatible ICS and ICS or LABA medications include Flovent [fluticasone], QVAR [budesonide], Advair MDI [fluticasone-salmeterol], Dulera [mometasone-formoterol], and Asmanex [mometasone-furoate]); (3) children and families must live or receive primary care in Philadelphia ZIP codes with the highest child asthma morbidity (greater than 100 pediatric asthma hospitalizations per year, according to Pennsylvania Health Care Cost Containment Council [22] hospitalization data); and (4) the parent or legal guardian must have a mobile phone plan with unlimited text messages.

Children will be excluded from the study if they are prescribed a controller inhaler to which the electronic device cannot affix (eg, any dry powder inhaler, Symbicort [budesonide or formoterol], or Seretide [fluticasone-salmeterol]) as their primary controller medication. Children with comorbid conditions that may influence the treatment of asthma (such as chronic lung disease, structural heart disease, or cystic fibrosis) will be excluded. Families will be excluded from the study if they have active state social services involvement or if they are non-English speaking. Subjects with significant developmental delays will also be ineligible.

### Outcome Measures

Given that this is a pilot study to assess the feasibility of a text message–based electronic adherence intervention in a vulnerable population, the primary outcomes will be feasibility oriented [23]. Feasibility outcomes will include (1) passive retention through the study and (2) perceived usefulness, acceptability, and preferences regarding the intervention components. Limited efficacy outcomes will include change in parent-reported asthma control and difference in average ICS adherence between the intervention and control conditions. Thirty-day readmissions and parent-reported adherence will be included as secondary outcome measures. Finally, medication use trajectories following hospitalization will be assessed using group-based trajectory modeling.

#### Feasibility

Feasibility will be assessed in 2 ways: (1) passive retention of participants in the intervention and follow-up phases, indicated by ongoing electronic sensor syncing and (2) text message and its usefulness, acceptability, and preferences, assessed via questionnaire. To assess passive retention, we will monitor duration of the interval that the electronic sensor synced with its receiver (either a mobile phone app or cellular hub). In order to sync effectively, the Bluetooth-enabled sensor must be within range of a functioning (plugged in) cellular hub or an open mobile phone app with Bluetooth enabled. Thus, passive retention represents whether the receiver was capable of transmitting MDI actuations from the sensor during the intervention and follow-up phases of the study. Reasons for missing actuation data will be collected during the follow up calls and during individual calls for participants whose sensors fail to sync within the first 2 days of the intervention phase of the study.

Perceived usefulness, acceptability, and intervention preferences will be measured using a 14-item questionnaire developed de novo for this study and delivered to those who receive the intervention either at follow-up call 1 or 2 (See Figure 1). This survey focused primarily on usefulness and acceptability of the daily text messages, as our prior work in a similar population found electronic sensors to be generally acceptable [24] (see Multimedia Appendix 1).

**Figure 1 figure1:**
[figure not shown]
Study flow diagram.

#### Limited Efficacy

Limited efficacy outcomes for this study will include (1) percent ICS adherence, as measured by electronic monitoring and (2) average change in parent-reported asthma control, assessed using the parent-reported portion of the child Asthma Control Test [25]. Inhaled controller medication use will be measured in both groups using electronic sensors (see description below) affixed atop of the MDI canister. ICS adherence will be calculated from the daily medication use data as the average percent adherence (observed actuations or prescribed actuations) for the intervention group versus the control group for the 30-day intervention phase. The average change in the parent-reported portion of the child Asthma Control Test score between enrollment and the 30-day follow-up call will be calculated for the intervention and control groups.

#### Adherence Trajectories

Finally, we will perform an exploratory analysis to assess for discrete trajectories of adherence using group-based trajectory modeling (GBTM). This analysis will include data from both the intervention and follow-up phases of the study. If no significant differences exist in limited efficacy outcomes between the intervention and control groups, data from both groups will be combined to produce pooled trajectory outcomes.

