### Intervention

#### Enrollment

Potential subjects will be screened through the daily census listings for the ED and general pediatrics inpatient units at CHOP, using the protocol inclusion and exclusion criteria. Parents of eligible participants will be approached for informed consent, screening, and enrollment prior to the patient’s discharge from the hospital. Child assent will be obtained from children ages 7 years and older, unless the child is judged to be incapable of assent. If subjects provide consent and enroll, they will complete the initial study visit prior to hospital or ED discharge. As part of enrollment, caregivers will complete an initial 30-minute survey on the Way to Health (WTH) platform (see below for description). Prior to survey completion, participants will be randomized into either the control or intervention group using a 1:1 randomization scheme, stratified by location (ED or inpatient). Each participant will be compensated US $20 through a reusable debit card following completion of each survey, for a total of US $60 for those completing the entire study.

Following the baseline survey, a study team member will attach an electronic sensor to the participant’s ICS inhaler. If the participants do not have a currently filled ICS prescription with them in the hospital room, they will be instructed on how to attach the sensor to the child’s inhaler when they get home. Participants whose sensors are not attached to the inhaler at discharge will be contacted by phone to achieve an initial sync. Participants who have mobile phones will download the Propeller mobile phone app for data transmission purposes, but the participants will not have access to any information from the app. Preferences for the text messages, which are delivered to the parents’ mobile phone via the Way to Health platform (time of day and preferred phone number), will be collected for all participants. Participants will be instructed to use the inhaler as directed by their physician and that they may begin to receive automated text message reminders regarding their child’s medication use.

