#### Limited Efficacy

Bivariate testing will be conducted to assess whether the intervention and control groups are balanced on key characteristics, including demographics, baseline asthma control (based on Child Asthma Control Test score on enrollment), and baseline medication adherence. If the groups are balanced, differences in 30-day adherence proportions and parental perceptions of asthma control between the intervention and control groups will be assessed using *t* tests or Wilcoxon Mann-Whitney tests depending on the distribution of the data. If the groups are unbalanced, regression models will be used to adjust for the unbalanced measured confounders.

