### Limitations

We anticipate several limitations of this study. Since the study is oriented to feasibility, the study is not powered to detect between-groups differences in adherence or adherence trajectories. Differences in actuation data, parent perception of asthma control, and medication use trajectories will be evaluated to assess trends for future efficacy testing.

Given the vulnerable nature of the patient population, researcher’s ability to contact caregivers for follow-up calls will limit both completion of the intervention and follow-up surveys and ongoing syncing. Many parents have changing work schedules that make it difficult to predict availability for follow-up calls in advance. Parents also frequently change their primary phone numbers, which limits follow-up and may affect whether they receive the text message intervention for the entire study period. We will reduce this limitation by asking participants for multiple contact numbers and recording preferred times to receive calls.

Most families in this study will go home with a new ICS prescription at discharge, however, the prescription is not always filled at the on-site pharmacy, so the sensor will not always be applied by study staff. In this circumstance, the caregiver must successfully fill the prescription at their pharmacy and correctly attach the electronic sensor themselves in order for actuation data to be available. To address this concern, research staff will conduct reminder calls in the few days following discharge. As a result of this limitation, actuation data at the front end of the intervention phase may be missing for some participants.

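### The exploratory trajectory model pools the arms when the efficacy tests are non-significant, though the protocol says the study is not powered for those differences

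*Protocol article*

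**What the plan says.** All references are to the protocol article.

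- **Pooling rule** (Adherence Trajectories): "If no significant differences exist in limited efficacy outcomes between the intervention and control groups, data from both groups will be combined" to give pooled trajectories. The same paragraph calls the analysis exploratory and says it uses data from both the intervention and the follow-up phase. What happens after a significant result is not stated.
- **Gating outcomes** (Outcome Measures, Limited Efficacy). The first is mean percent adherence, "for the intervention group versus the control group for the 30-day intervention phase". The second is the "average change in parent-reported asthma control, assessed using the parent-reported portion of the child Asthma Control Test", measured from enrolment to the 30-day call.
- **Tests** (Data Analysis, Limited Efficacy): t tests or "Wilcoxon Mann-Whitney tests depending on the distribution of the data", with regression if the arms are unbalanced. No significance level is given.
- **Power** (Limitations): "the study is not powered to detect between-groups differences in adherence or adherence trajectories". The next sentence says that differences, including those in medication-use trajectories, will still be examined for trends.
- **Size** (Participants): "Participants will include 40 children aged 2 to 13 years and their parent or legal guardian", allocated 1:1 (Enrollment).
- **Exposure after day 30** (Abstract, Methods): in the follow-up phase "all participants may choose whether or not to receive the text messages".
- **Model** (Data Analysis, Trajectories): solutions with 3, 4, 5 and 6 groups are compared, and the chosen groups serve to describe qualitative trends.

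**The concern.** The rule treats failure to reject as evidence that the arms do not differ. That inference needs a test with good power against differences that matter, and the protocol says it does not have one.

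The gate also looks at something other than what it controls. Two arms can have the same mean adherence over 30 days and different courses within those days, or they can diverge later. A 30-day mean and a 30-day change in a control score say nothing about days 31 to 60.

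Finally, Limitations intends to look at trajectory differences, while the pooling rule provides for arms to be combined without saying that arm will still be reported. The two statements need to be reconciled. At stake is how the trajectory groups can be read. The Discussion wants them to show how, when and why inhaled corticosteroid use falls off after an exacerbation. If groups come from a combined sample with arm left out, a reader cannot tell how far they reflect reminders.

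**Working it through.** **Plan's own figure.** There is none to reproduce. The article gives no power, alpha, SD or effect size, and 40 is not derived from a calculation.

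**Inputs from the article.** N = 40 at 1:1, so n = 20 per arm. Two gating outcomes. t test or rank test.

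**Assumptions.** Two-sided alpha 0.05. Adherence SD 30 percentage points (range 25 to 35). Limitations expects some missing actuation data but gives no rate, so n = 15 per arm (25% loss) is also shown.

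**Step 1: adherence test alone.** The noncentrality is λ = Δ / (SD × √(2/n)), and power is the probability that a noncentral t with 2n − 2 degrees of freedom exceeds the critical value in absolute size. For Δ = 15 and n = 20, √(2/20) = 0.316, with 38 degrees of freedom:

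| Assumed SD | λ | Power | Non-significant |
|---|---|---|---|
| 25 | 15/7.91 = 1.90 | 46% | 54% |
| 30 | 15/9.49 = 1.58 | 34% | 66% |
| 35 | 15/11.07 = 1.36 | 26% | 74% |

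Power of 80% needs 0.91 SD, which is 0.909 × 30 = 27 points (23 at SD 25, 32 at SD 35). Non-significance is more likely than not for true effects below 0.64 SD with 20 per arm, or below 0.74 SD with 15 per arm.

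**Step 2: both outcomes, as the rule reads.** Pooling follows when neither outcome is significant. This was simulated with t tests on normal data, 20,000 trials per scenario, correlation 0 or 0.5 between outcomes, and a true asthma-control effect of 0 or 0.3 SD. Ranges cover those settings.

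| True adherence effect | Pooled, 20 per arm | Pooled, 15 per arm |
|---|---|---|
| 0.3 SD | 72–81% | 77–84% |
| 0.5 SD | 56–64% | 65–71% |
| 0.8 SD | 26–30% | 38–43% |
| 1.0 SD | 11–13% | 22–24% |

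With no true effect on either outcome, pooling occurs in about 91% of trials. At 0.5 SD and 20 per arm it still occurs in 56–64%, so a non-significant result separates these two situations poorly.

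**Step 3: time window.** The gate covers days 1 to 30. The model covers both phases, up to day 60. After the first follow-up call either arm may take reminders, so from then on randomised arm no longer equals exposure.

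**The case against.** The strongest defence is one of scale and candour. The analysis is labelled exploratory, the primary outcomes concern feasibility, and the trajectory groups are meant only to suggest qualitative trends for later study. The lack of power is disclosed, and a look at trajectory differences is already intended. All of that stands. It limits the weight of the point but does not make the gate valid.

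Pooling itself is not the error. One model for all 40 children is reasonable and is what the fix keeps. The error is that a test result decides whether to pool, with no commitment to show arm afterwards.

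Four stronger readings are tempting, and the document does not support them:

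- *That the arms will usually be pooled despite a real effect.* This depends on an SD and an effect size that the article does not give. It holds for small and moderate effects. At 0.8 SD pooling becomes the less likely outcome, and the Introduction describes the earlier trials' improvements as dramatic.
- *That the children are merged into one pattern, hiding any effect of the texts.* The arms would form one sample, from which 3 to 6 groups are fitted. A course driven by reminders could appear as its own group.
- *That the protocol presents pooled trajectories as untreated decay.* It does not say so, and the Discussion expects decay to vary between families.
- *That a significant result leads to separate models by arm with very small groups.* The article does not state that branch, and one model with arm reported would fit the text equally well.

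**Conclusion.** The point holds as a flaw in a stated decision rule. Non-significance in a study declared not powered for the comparison is used as the condition for combining arms, on outcomes that cover only the first 30 days of a model running up to 60. The rule also sits awkwardly with the stated intention to examine trajectory differences.

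The logical fault needs no assumption about effect size; how often it would matter does. Under the assumptions above, a true 15-point effect would be missed on adherence in about two trials in three, and pooling would follow in somewhat over half of trials at 0.5 SD but in fewer than a third at 0.8 SD with 20 per arm. A general claim that pooling will usually mask a real effect therefore goes beyond the document. The consequence is confined to the interpretation of an exploratory analysis and is worth correcting because correction is nearly free.

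**What to change.** Remove the significance condition from Adherence Trajectories and state, whatever the efficacy tests show:

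1. One trajectory model is fitted to all participants with data.
2. Trajectory-group membership and observed daily adherence curves are reported by randomised arm.
3. Days after the first follow-up call are also described by reminder choice (on or off). This is descriptive only, because the choice is self-selected.
4. The fitted groups are described as a mix of reminder-exposed and unexposed children.

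Entering reminder status as a time-varying covariate is not advised. After the first call it is self-selected, it would add parameters in 40 children, and the platform's on/off setting governs sending, not receipt. Limitations itself warns that changed phone numbers may affect delivery.

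The cost is a wording change and some extra reporting. Randomisation and the on/off switch already run through the Way to Health platform, so no new data should be needed. The downside is that by-arm counts will be small and imprecise: with 3 to 6 groups of equal size, about 20/6 = 3 to 20/3 = 7 children per arm in each. They should be shown as counts, without tests.
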